### Randomisation

Randomisation was carried out centrally by the trial statistician, using a partial minimisation procedure that dynamically adjusted the randomisation probabilities in order to balance important covariates; body mass index, sex, age, physical activity (individually calibrated heart rate monitoring, see below), family size, and behavioural intentions. Randomisation thus used baseline measures. Thirty-two pairs of siblings and two sibling-triples were cluster randomised to the same study group to avoid contamination, and the remaining 295 participants (81%) were individually randomised. Overall, 365/465 (78%) of those eligible went forward to randomisation.

### Baseline measures and follow-up

At baseline and the end of the study, all participants attend the study centre at either Ely or Cambridge for questionnaires, physiological and anthropometrical measures, and venesection. At six months, psychological and self-reported physical activity data are collected by postal questionnaires. Measures relating to the intervention programme evaluation are collected by the facilitators during the intervention, and we assess reported use of self-regulatory strategies by participants to increase their activity levels at six and twelve months.

### Compliance with follow-up

In similar primary care based trials we have achieved attrition rates of 30% or less [38,39], and at current rates we will exceed the required 300 to complete the study (100 in each group, see Figure 1).

Maximising retention is an important issue, particularly as the comparison group do not benefit from regular contact with a facilitator. At recruitment, the introductory leaflets for all three arms emphasised the importance of follow-up, irrespective of treatment group. Participants who drop out of the intervention programme are contacted by a principal investigator, and offered an opportunity to give feedback and to confirm drop out from the intervention programme only, or from trial measurement as well.

### Measurement

The distribution of measures across baseline, six-month and one-year follow-up are shown in Table 1. The principle outcome is an objective measurement of physical activity energy expenditure, the daytime physical activity ratio (dayPAR), which is the ratio of daytime energy expenditure to resting energy expenditure measured using heart rate monitoring with individual calibration for the heart rate-energy expenditure relationship [40,41]. This allows more precise quantification of the relationship between energy expenditure and relevant disease end points than self-report [13]. The method has been validated against the gold standard techniques of doubly-labelled water and whole-body calorimetry [42]. Physical activity is also measured by a validated questionnaire covering work, recreation and domestic activity over the previous month and year [43], and offspring report of usual physical activity patterns among family members and how they changed over the previous year.

**Table 1 T1:** Study measures

**Measures**	**Baseline**	**6 months**	**12 months**
**Questionnaire measures:**			
1. Godin / EPIC self-reported physical activity [36]			
2. Short form State anxiety [45]			
3. Risk / worry diabetes^+^			
4. Theory of Planned Behaviour [24]^+^			
5. General Questionnaire, comprising:			
A) Rose Angina questionnaire			
B) Smoking, Alcohol & Physical Activity^+^			**(smoking &** **physical activity ** **only)**
C) Occupation & Social Class			
D) SF-36 & EQ-5D [44,46]			
6. EPAQ (2) [43]			
7. Clinical measurement questionnaire (physiological measures and family history)			
8. Physical activity of family members^+^			
9. Injury questionnaire^+^			
10. Intervention programme satisfaction^+^*			
11. Skills acquisition^+^*			
**Physiological measures: **[13,40-42,51]			
Cardiorespiratory fitness & dayPAR parameters			
Weight, height, % body fat, blood pressure, ECG			
Biochemical parameters (fasting plasma glucose, glycosylated haemoglobin, insulin, lipids)			
Blood stored for future genetic testing			
**Costs:**			
Cost to the NHS of facilitator training & salary^+^			
Costs of intervention programme delivery^+^			

^+ ^questionnaires developed for study

* intervention programme participants only

Oxygen uptake (ml O_2_/kg/body weight) is measured by indirect calorimetry during a submaximal graded treadmill exercise test, and maximal cardiorespiratory fitness (VO_2max_) is estimated using predicted maximal heart rate (i.e. 220 minus age) [40,42].

Self-report measures of well-being and quality of life include subjective health and energy (SF-36) [44], anxiety [45], worry about diabetes and perceived vulnerability, and EuroQol (EQ-5D) [46].

The frequency and severity of physical activity related injury is assessed by study questionnaire at one year.

Psychological mediators of physical activity include intention to increase activity over the next year, and its predictors (attitude, subjective norm, perceived behavioural control). These key measures have been developed for the study following the recommendations of Ajzen [24]. Physiological correlates of behaviour include weight measured on standard scales calibrated at three monthly intervals, body fat percentage measured by bio-electrical impedance (Bodystat, Isle of Man, UK), and systolic/diastolic blood pressure, measured using an automatic sphygmomanometer (Accutorr, UK). Biochemical correlates include fasting plasma glucose, glycosylated haemoglobin, insulin and lipids. We are storing EDTA whole blood samples for future genetic testing. Sociodemographic factors and ECG are also documented at baseline.

### Cost of the intervention

The economic analysis will explore the impact of a physical activity intervention programme on NHS costs. As the study is explanatory in design, we will not conduct a full cost-effectiveness analysis, but aim to provide a cost-description of the delivery of the intervention programmes. We are measuring the costs of delivering the 'face-to-face' and 'distance' intervention programmes via family health facilitators. These costs primarily comprise the training of facilitators, educational materials, travel, and the time that facilitators spend contacting and visiting families (including cancelled visits). Travel costs and contact time are recorded by the facilitators for every trial participant. The cost of facilitator time will be based on national average salaries, employment costs, qualifications, overheads and indirect costs [47]. Although we do not expect the ***ProActive ***intervention programme to have an impact on health service costs in the short term, we are monitoring health service utilisation (hospital, primary and community care) in the last 20% of participants recruited to the study.

### Participant safety

The primary safety concerns for participants in ***ProActive ***are cardiovascular and musculoskeletal events associated with the laboratory procedures of treadmill exercise testing and injuries sustained as a consequence of increasing physical activity in everyday life. The cardiorespiratory fitness test used in this study is submaximal, and only undertaken following extensive screening procedures. If a participant exhibits a positive Rose angina questionnaire [48], a positive physical activity readiness questionnaire [49] or an abnormal ECG, they are referred to a clinical member of the measurement team for a more detailed medical review. If there are clinical concerns, participants are excluded from the study, and referred to their general practitioner. In over 3000 such tests undertaken by our group using this protocol, no significant adverse events have occurred. Supervising staff are trained and hold current cardio pulmonary resuscitation certificates.

Ranges for acceptable results are set for all clinical measures. If these are exceeded, the information is sent to the general practitioner, and the participant informed and advised to consult.

As the intervention programme is based on participants' own preferred activities, and emphasises small achievable goals set by the participants, the risk of excess injury is small. Group information about injury will be reported.

Participants previously unaware of their familial risk of diabetes may experience anxiety related to awareness of their increased risk status. This is considered in facilitator training, and measures of anxiety, worry about diabetes and perceived vulnerability are included (see above).

### Data management, quality assurance and exclusion of bias

Physiological and anthropometric measures are made in two centres by observers unaware of individuals' group allocation. Biochemical measures are made in one laboratory with established quality assurance systems. Randomisation was undertaken by the trial statistician, independently of the trial co-ordination team, and the data entry team are unaware of study group.

The administrative database (participant information), dayPAR values and blood test results are managed in-house, with the latter being double entered. Numeric fields have limiters set so that values outside a defined range cannot be entered. Additionally, any blood results outside the 'normal range' are flagged for confirmation of value. Random checks on administrative data are performed regularly, checking the data on the database against paper records and correcting any errors found.

Double data entry of all anthropometric and questionnaire measures is undertaken by an experienced, independent agency, blind to study group (Wyman Dillon Research and Data Management, Bristol, UK). In addition, random checks are applied as described above.

### Intervention (see Figure 1)

#### Intervention programme contacts

The family health facilitator contacts participants randomised to the 'face-to-face' and 'distance' interventions, and arranges a home interview including family members. At this introductory interview, personal reasons for increasing physical activity are elicited and reinforced, family participation is encouraged, and the relationships between physical activity, weight gain and prevention of Type 2 diabetes are explained and discussed.

In the 'face-to-face' arm this is followed by four visits and two brief support telephone calls over five months. During these interactions the participant and willing family members learn strategies to increase physical activity, for instance selecting activities that they enjoy doing, setting achievable goals, defining action plans, self-monitoring, self-reinforcement and relapse prevention. Pedometers are available for self-monitoring among participants who have chosen walking as their goal. A key difference between this intervention and others currently under evaluation (e.g. ACT) is that there is no absolute target for physical activity defined at the outset. Family members are encouraged to make gradual and continuous increases in their activity, as much as they feel able to, on the understanding that all increases, if maintained, are beneficial. Follow-up continues by monthly telephone calls up to one year, to discuss any difficulties in applying the strategies, and to encourage family members to increase activity further.

In the 'distance' arm, following the introductory meeting the intervention programme is delivered by six telephone calls over five months, and then monthly by post up to one year, with content similar to the 'face-to-face' arm. During the phone calls the facilitators encourage the participants to involve family members. Visits and telephone calls take approximately one hour and 45 minutes, respectively.

#### Materials

An arm-specific introductory leaflet is used, but otherwise materials are the same for the face-to-face and distance arms. All introductory leaflets include text to encourage retention in the trial. In the comparison arm the leaflets offer brief advice on the benefits of physical activity. Participants in the intervention programme arms are given an educational manual describing the strategies that participants are encouraged to use to increase their habitual activity in a step by step fashion.

#### Promotion of fidelity of intervention delivery

Various mechanisms are used to promote the fidelity of delivery of the intervention programme to the underlying psychological theories and intervention programme protocols. A detailed training manual and protocols for each contact were developed, and a Training Officer appointed. Facilitators attended a five day phased course in psychological theories, behaviour change techniques and experiential training in techniques, with six half-days initially, followed by refresher sessions at six months and continuing supervised practice by a clinical psychologist and through peer-appraisal. Facilitators complete a checklist for the introduction of and mastery of self-regulatory strategies by the participant after each contact, and monitor intervention programme attendance and drop-out for each participant.

#### Assessment of fidelity and evaluation of the intervention programme

An assessment of adherence by facilitators to the behaviour change techniques specified in the protocols was conducted among a random sample of 27 participants, using reliable coding frames and transcripts of the sessions. The intervention programme evaluation includes: an assessment of the frequency of meetings and telephone calls, proportion of progress reports and postcards sent and progress reports returned, satisfaction with the intervention programme, reported use of self-regulatory strategies by participants at six months and one year, and drop-outs at one year.

## Statistical procedures

### Sample size

The sample size calculation was initially based on physical activity level (PAL), the ratio of total energy expenditure to estimated basal metabolic rate [40,41], and required 100 individuals completing one-year follow-up in each group. Prior to the measurement of any follow-up data, and endorsed by the Trial Steering Committee, a proposal was made to change the primary outcome measure to dayPAR, the ratio of daytime energy expenditure to resting energy expenditure, on grounds that this outcome consisted entirely of measured rather than estimated quantities. The calculations were based on the Ely cohort study data [41,50], in which the residual standard deviation of one-year change in dayPAR adjusting for baseline was 0.53. With 100 individuals in each group, there is 80% power to detect a difference in mean dayPAR of 0.18 between the combined intervention programme groups and the control group with a two-sided test at the 5% level of significance. This is equivalent to 2 MET hours/day, 30 minutes of brisk walking on the level, or 20 minutes of leisurely bicycling or swimming; a plausible and important increase. The observed difference in mean dayPAR between any pair of groups will be estimated with a 95% confidence interval having the width ± 0.15, equivalent to ± 1.75 MET hours/day, ± 25 minutes brisk walking or ± 15 minutes bicycling or swimming. Calculations were based on equal numbers in each group, and require 300 participants with outcome data at one-year follow-up. Recruitment of 400 participants allowed for 25% attrition after randomisation, and lower interim attrition rates will enable a lower recruitment target of 365 participants (Figure 1).

Main analyses will be at one year, comparing combined 'face-to-face' and 'distance' versions of the intervention programme with 'brief advice', comparing 'face-to-face' with 'distance' modes of the intervention programme, and estimating the difference between each intervention programme group and 'brief advice' to inform a larger pragmatic trial. Analysis by intention-to-treat will retain individuals within their randomised group regardless of participation. Comparisons will involve an adjustment for baseline physical activity and other variables used in the randomisation. We will undertake sensitivity analyses, assuming a range of potential outcomes for non-completers, informed by available baseline and interim data on non-completers. Non-completers will have multiple data imputed with a 'missing at random' assumption and with sensitivity analyses to represent optimistic and pessimistic scenarios for drop out. Clustering effects by family will be estimated for the primary outcome.

A secondary 'dose-response' analysis will use all three randomised groups, over baseline, six months and one year. A 'per protocol' analysis will also be undertaken among those completing the intervention programme.

The incremental cost of delivering the 'face-to-face' intervention programme will be compared to the 'distance' and 'brief advice' groups.

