#### (ii) Attention to adoption and maintenance of physical activity

A range of behaviour change techniques with evidence for their effectiveness was used to bridge the gap between intention and action: goal setting and review, action planning, use of prompts, self-monitoring, and reinforcement [2,18,23,25]. Use of a causal model, linking measured beliefs and attitudes to behaviour will allow subsequent process analysis to better specify both determinants and intervention (Hardeman *et al*., 2004. A causal modelling approach to the development of theory-based behaviour change programmes for trial evaluation. Submitted).

Major challenges in promoting physical activity are maintenance of behaviour change, and the avoidance of drop out rates that can approach 50% [5,26]. Reviews suggest that theoretical advances in facilitating behaviour maintenance have not been applied in intervention programmes [27,28]. The highest levels of participation have been achieved by home-based interventions, involving frequent professional contact, and promoting enjoyable, informal exercise of moderate intensity, such as walking [2,8]. Behavioural maintenance may be best supported by building habits, using self-regulatory strategies such as repetition of behaviours over time in a constant environment, ongoing goal review, self-monitoring, reinforcement, and relapse prevention [28,29]. The use of mail and telephone contacts is a promising cost-effective approach [23], especially the use of frequent, brief, support calls [2]. All these approaches are incorporated into ***ProActive***.

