## Methods/design

***ProActive ***is a four-year study with a complex randomised trial design [30], with central randomisation of willing participants to intervention programmes or comparison. The trial is managed from the Institute of Public Health, University of Cambridge, following MRC guidelines. Ethical approval has been obtained from the Eastern MREC, and West Suffolk, Cambridge, Huntingdon and West Essex LRECs.

The study design and patient flows (achieved at recruitment closure, October 2003, and projected to end of study) are shown in Figure 1. The focus of measurement is the adult offspring of a Type 2 diabetic parent, but the focus of the intervention programme is this individual within a family context. Participants were recruited via parents with diabetes on primary care registers (20 practices), or directly through records of their family history of diabetes (seven of the 20 practices). Sedentary individuals and their families were randomised to facilitation, either 'face-to-face' or 'distance', or to a comparison arm offering a leaflet providing brief advice on the benefits of activity. Psychological, physiological, anthropometric and biochemical data were collected at baseline and one year after randomisation, with psychological data also collected at six months after randomisation.

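### The per-protocol analysis selects on programme completion, which exists in only two of the three arms, and names no comparator; set against brief advice it would be non-randomised and open to selection bias

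*Protocol article*

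**What the plan says.** After the sample size text, the statistical section of the protocol article sets out an intention-to-treat main analysis: "Analysis by intention-to-treat will retain individuals within their randomised group regardless of participation". It then adds a secondary analysis: "A 'per protocol' analysis will also be undertaken among those completing the intervention programme". No comparator is named for it.

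Other sections show who can meet the completion condition:

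- Intervention programme contacts: "The family health facilitator contacts participants randomised to the 'face-to-face' and 'distance' interventions, and arranges a home interview including family members". The visits, calls and postal contacts that follow belong to these two arms only.
- Methods/design: the alternative to facilitation was allocation "or to a comparison arm offering a leaflet providing brief advice on the benefits of activity".
- Compliance with follow-up: "the comparison group do not benefit from regular contact with a facilitator".

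Two further statements bear on the remedy. Facilitators "monitor intervention programme attendance and drop-out for each participant" (Promotion of fidelity of intervention delivery). Those who leave the programme are asked "to confirm drop out from the intervention programme only, or from trial measurement as well" (Compliance with follow-up), so leaving the programme does not by itself mean losing the outcome.

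**The concern.** Staying with a year of contacts plausibly reflects motivation, health and spare time, each of which may also predict activity at one year. If the programme arms are cut down to completers while brief advice stays whole, the groups differ in these respects even when the programme does nothing. No matching restriction is possible in brief advice, because that arm has nothing to complete.

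The trial describes itself as explanatory and as an efficacy trial, and its estimates are meant to inform a larger pragmatic trial. Readers will look to this analysis for the effect in people who took the programme up. A spurious difference there could be carried into the planning of the next trial.

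**Working it through.** **Inputs from the protocol article (Sample size).** Residual SD of one-year change in dayPAR, adjusted for baseline, 0.53. Target difference 0.18. 100 per group with outcome data, so 200 v 100 for combined programme against brief advice. Two-sided 5%.

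**The plan's own figure.** SE = 0.53 × √(1/100 + 1/200) = 0.0649. Power ≈ Φ(0.18/0.0649 − 1.96) = Φ(0.81) = 79%, against the stated 80%. The figure reproduces, so 0.53 and 0.18 are a fair scale for the bias. The article gives no figure for the per-protocol analysis.

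**Assumptions not in the article.** The true effect is zero. Completers are compared with all of brief advice. Completion occurs when a normal latent propensity exceeds a threshold. Its correlation r with the one-year outcome is what remains after the planned baseline adjustment. The completion rate c runs from 50% to 90%. The lower end borrows from the Background, which names among the challenges of the field "the avoidance of drop out rates that can approach 50" per cent.

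**Formula.** With t = Φ⁻¹(1 − c) and λ = φ(t)/c, bias = r × λ × 0.53. For the false-positive rate, the completers' variance is v = 0.53² × [1 − r²λ(λ − t)], SE = √(0.53²/100 + v/(200c)), and bias/SE is referred to the two-sided 1.96 limits.

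Example, c = 0.7 and r = 0.2: t = −0.524, λ = 0.348/0.7 = 0.497, bias = 0.2 × 0.497 × 0.53 = 0.053, or 0.053/0.18 = 29% of the target.

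| Completion c | λ | Bias, r = 0.2 | False-positive rate | Bias, r = 0.3 | False-positive rate |
|---|---|---|---|---|---|
| 90% | 0.195 | +0.021 | 6.1% | +0.031 | 7.6% |
| 80% | 0.350 | +0.037 | 8.5% | +0.056 | 13.2% |
| 70% | 0.497 | +0.053 | 11.9% | +0.079 | 21.0% |
| 50% | 0.798 | +0.085 | 20.6% | +0.127 | 40.4% |

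At r = 0 the bias is 0 and the rate stays at 5%. At r = −0.2 the sign reverses (−0.021 to −0.085).

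**Cross-check without the normal model.** If completers and non-completers differ by D in dayPAR for reasons other than the programme, bias = (1 − c) × D. With D = 0.18 this gives 0.018, 0.036, 0.054 and 0.090 at 90%, 80%, 70% and 50% completion, the same order as the r = 0.2 column.

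**The case against.** The strongest reply is that the contrast examined here is not written in the article. The sentence names no comparator. Read literally, it could mean face-to-face completers against distance completers, since the comparison of those two modes is among the main analyses. The exact definition of completion and of the comparator may also sit in an analysis plan that is not shown, and their absence from an article is no fault. This stands as a limit: a reader might infer that completers will be compared with all of brief advice, but the article does not say so. What the article does fix is the selection rule. That rule cannot be applied in brief advice. A comparison between the two programme arms would also be between groups selected under different contact schedules.

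Second, a reader might infer that the analysis is biased towards the programme as a matter of fact. The article has no data on how completion relates to outcome. It also plans to adjust comparisons for baseline activity and the other minimisation variables, which include behavioural intentions, a direct measure of motivation. That adjustment may shrink the bias. It cannot be relied on to remove selection that arises after randomisation.

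Third, the figure near 50% describes the field and a problem this trial was designed to avoid. The trial's own attrition figures (30% or less in similar trials, a 25% allowance) concern follow-up, not programme completion. At 80% to 90% completion and r = 0.2 the bias is only about 0.02 to 0.04.

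Fourth, an instrumental-variable analysis has its own weak point. With completed yes/no as the exposure, it assumes that people who leave the programme gained nothing, although they may have had the introductory interview, several contacts and the manual. This objection is sound and shapes the choice of exposure in the fix.

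**Conclusion.** The concern holds in a conditional form. The per-protocol set is defined by a post-randomisation condition available in two of three arms, and no comparator is stated. If completers are set against brief advice, the contrast is non-randomised and open to selection bias, probably in the programme's favour. Under no true effect, r of 0.2 to 0.3 and 50% to 90% completion, the bias is about +0.02 to +0.13 dayPAR, or roughly 11% to 70% of the 0.18 target. The upper end needs both the lowest completion rate and the higher correlation. Both r and the completion rate are assumptions.

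The documents do not support a reading that the trial's primary conclusion is at risk. The main analysis is by intention to treat, and no sample size or main contrast depends on the completer analysis. The point deserves a change because the selection rule is poor and a better method can use data already being collected.

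**What to change.** Estimate the effect in those who took up the programme with a complier-average (instrumental-variable) analysis of one-year dayPAR:

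- Keep all randomised participants, with randomised arm as the instrument.
- Use the attendance that facilitators log as the exposure, preferably any uptake or the number of contacts by arm. Keep contacts separate by arm because visits, calls and post differ.
- Use binary completion only as a sensitivity analysis, since partial attenders may benefit.
- Keep the stated baseline covariates and allow for clustering by family.

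If a completer contrast is still shown, name its comparator and label it exploratory and non-randomised.

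**Cost.** Analysis work only, with no new data collection. The interval widens. As a rough guide with binary exposure at 70% completion, the intention-to-treat half-width of 1.96 × 0.0649 = 0.127 becomes 0.127/0.7 = 0.18. The completer contrast would give about 1.96 × 0.53 × √(1/100 + 1/140) = 0.136, narrower but around a possibly biased value. The estimate relies on the exclusion restriction, that allocation acts on the outcome only through the exposure used. Contact count also assumes a linear effect per contact. If nearly everyone has some uptake, the any-uptake estimate will lie close to intention to treat.
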